| Number of Participants with Rationale | 
According to a recent randomized trial including a series of PD and assessing a realimentation process (enteral vs. parenteral), the mean CCI was impacted by about 30% (32.8 vs. 24.2). Another study reported a mean CCI of 38 after PD. We hypothesized that ENN would reduce a mean CCI of 35 (± 20) by 30%.
 
Assuming a CCI reduction of 10.5 points (30% of 35), a standard deviation of ± 20, a 80% power, an alpha of 5% and a dropout rate of 20%, the total required number of patients is 144 (72 study patients = EEN group and 72 control patients = oral nutrition group).
                                                                                                                                                                                                                                                                                                                                                                                                                                                                                                                                                                                                                                                                                                                                                                                                                |
| Study Intervention                    | 
In our current practice, no feeding or suction gastric tube is left in place after PD. Patients will receive standardized perioperative care according to the Enhanced Recovery After Surgery protocol. A standard nutrition protocol for the EEN intervention group has been established in accordance with the nutritionists:
 
The night after the operation, a low flow enteral nutrition will be initiated (21 ml/h, 250 ml/12 h), and based on an Isosource® Energy Fibre solution (hypercaloric).
 
If the tolerance is subjectively good, with a visual analogue scale ≤4/10, the flow will be increased on postoperative day (POD) 1, at the flow of 42 ml/h (500 ml/12 h).
 
On POD 2: increased flow to 62.5 ml/h (750 ml/12 h).
 
On POD 3: increased flow to 83.5 ml/h (1000 ml/12 h).
 
If the tolerance is not satisfactory (>4/10), the current flow will be decreased, maintained 24 hours more or put on hold for a couple of hours according to the symptoms of the patient.
 
The nutrition will be infused over 12 hours with a pump and controlled flow rate. Enteral nutrition will be continued until oral food intake reaches 50% of nutritional requirements defined as 30 kcal/kg/day for patients with BMI <30 kg/m^2 or 25 kcal/kg/day for patients with BMI ≥30 kg/m^2 (oral intake will be assessed by the dietician).
 |

|                                    |                                                                                                                                                                                                                                                                                                                                                                                                                                                                                                                                                                                                                                                                                                                                                                                                     |
|------------------------------------|-----------------------------------------------------------------------------------------------------------------------------------------------------------------------------------------------------------------------------------------------------------------------------------------------------------------------------------------------------------------------------------------------------------------------------------------------------------------------------------------------------------------------------------------------------------------------------------------------------------------------------------------------------------------------------------------------------------------------------------------------------------------------------------------------------|
| Control Intervention        | The control group will receive oral nutrition after the operation as it is presently done in our division based on our clinical care maps.                                                                                                                                                                                                                                                                                                                                                                                                                                                                                                                                                                                                                                                          |
| Study procedure             | At the end of surgery, a polyurethane single or double-lumen feeding nasojejunal tube (Freka®) 8 French will be placed under direct visual control, 30 cm distally to gastrojejunostomy, in patients randomized to EEN. The tube will be attached to the nose wing with a tape according to current institutional practice.                                                                                                                                                                                                                                                                                                                                                                                                                                                                         |
| Study Duration and Schedule | Three years
Planned date of first participant-in: October 2021
Planned date of last-participant-out: October 2024                                                                                                                                                                                                                                                                                                                                                                                                                                                                                                                                                                                                                                                                             |
| Main Investigators          | [name], Visceral Surgery, Centre hospitalier universitaire vaudois, CHUV
[name], Visceral Surgery, Centre hospitalier universitaire vaudois, CHUV
[name], Visceral Surgery, Centre hospitalier universitaire vaudois, CHUV
[name], Visceral Surgery, Centre hospitalier universitaire vaudois, CHUV
[name], Visceral Surgery, Centre hospitalier universitaire vaudois, CHUV                                                                                                                                                                                                                                                                                                                                        |
| Study Centers               | Centre hospitalier universitaire vaudois, CHUV
[name]
[name]

Hôpital Cochin – Port Royal, AP-HP
[name]
[name]

Regional Hospital of Lugano
[name]
[name]                                                                                                                                                                                                                                                                                                                                                                                                                                                                                             |
| Data privacy                | The investigators affirm and uphold the principle of the participant's right to privacy and that they will comply with applicable privacy laws. Especially, anonymity of the participants will be guaranteed when presenting the data at scientific meetings or publishing them in scientific journals.

Individual subject medical information obtained as a result of this study is considered confidential and disclosure to third parties is prohibited. Subject confidentiality will be further ensured by utilizing subject identification code numbers to correspond to treatment data in the computer files.                                                                                                                                                                          |
| Ethical consideration       | The goal of this study is to define the best route for nutrition after PD. The method of randomization will permit to have a high level of evidence.

There are several adverse effects associated with nasojejunal tube and enteral nutrition as mentioned above in the risk-benefit section. Nurses and doctors of our division are nevertheless used to this equipment, frequently used in visceral surgery. The risk of adverse events associated with the study is therefore judged as low.

From the investigators' perspective, the EEN intervention is hypothesized to benefit patients. Nevertheless, the control group cannot be considered as unfavored as the current nutritional management consists of oral nutrition.

No vulnerable populations will be included. |

|                      |                                                                                                                                                                                                             |
|----------------------|-------------------------------------------------------------------------------------------------------------------------------------------------------------------------------------------------------------|
| GCP Statement | This study will be conducted in compliance with the protocol, the current version of the Declaration of Helsinki, the ICH-GCP, the HRA as well as other locally relevant legal and regulatory requirements. |
|----------------------|-------------------------------------------------------------------------------------------------------------------------------------------------------------------------------------------------------------|

## 2 BACKGROUND AND RATIONALE

Pancreatic cancer (PAC) is one of the deadliest cancers in humans (more than 47'000 estimated deaths in 2020 in the United States). It is predicted to become the second most common cause of cancer deaths in the United States by 2030^2. The mean costs in 2015 were estimated to be \$79'800 per patient with PAC and \$164'100 for each resection. The observed overall 3-year survival after diagnosis is 6%. The majority of PAC are adenocarcinomas and approximately 60-70% of them are localized in the head of the pancreas. To date, surgery remains the only potentially curative strategy. However, resection of the pancreatic head remains a difficult surgical procedure embedded with high morbidity (40-60%). Recently, the concept of Enhanced Recovery After Surgery (ERAS) has contributed to reduce overall morbidity, length of hospital stay and costs by implementing multimodal measures influencing the pre-, intra- and postoperative periods.

Patients suffering from pancreatic tumors as well as patients with chronic pancreatitis often present with cachexia or at least with a certain level of malnutrition. This situation is difficult to correct preoperatively due to the pressure to operate these patients rapidly. Nutritional therapy should therefore be started early during the postoperative course to prevent further malnutrition, as the latter is an important risk factor to develop complications. This is even more relevant for patients with poor preoperative nutritional status. In addition, surgery disrupts the digestive tract, leading to postoperative indigestion and malabsorption. Postoperative nutritional supports, including early enteral nutrition (EEN) and total parenteral nutrition (TPN), have been shown to be effective in improving clinical outcomes after major abdominal surgery.

Malnutrition is still poorly defined. Many definitions have been proposed based on criteria that vary between medical history, biometric and biological data. Currently, the European Society for Parenteral and Enteral Nutrition (ESPEN) recommends the Nutritional Risk Score (NRS-2002) as a screening tool, even if it has not been prospectively validated. Several studies have proven its reliability to identify patients at nutritional risk who will benefit from perioperative nutritional support. Patients with NRS  $\geq 3$  are considered to be exposed to higher incidence and severity of postoperative complications.

Recent randomized clinical trials and meta-analyses have shown that EEN could shorten length of stay, reduce postoperative infections and mortality and improve cost-effectiveness when compared to TPN in gastrointestinal cancer surgery. Specifically after

pancreatoduodenectomy (PD), EEN reduces early and late complications, infections, and readmission rates. Another retrospective study showed no differences with respect to time to resumption of normal oral intake, morbidity and mortality when comparing EEN via nasojejunal tube or jejunostomy tube and total parenteral nutrition. However, a recent multicentric randomized controlled trial compared nasojejunal EEN to TPN after PD. This study showed that EEN was associated with an increase of overall postoperative complications. One major drawback of this study is that it did not compare EEN to the recognized standard which is oral feeding and not TPN. Another systematic review compared the outcomes of 5 feeding routes after PD (oral diet, enteral nutrition via either a nasojejunal, gastrojejunostomy tube or jejunostomy tube, and TPN) and reported no evidence to support routine enteral or parenteral feeding after PD.

The study of EEN and its impact in terms of morbidity require the use of a validated tool. Most studies fail to provide information about the severity of complications and inform only on the most severe event, ignoring events of lesser severity. The Comprehensive Complication Index (CCI) was created to summarize all postoperative complications and is more sensitive than existing morbidity endpoints.

The primary objective of the study is to assess the impact of EEN on postoperative morbidity after PD, according to the CCI. Secondary objectives are to assess the impact of EEN on major postoperative complications, according to Clavien classification, specific complications, length of stay, readmission rates, quality of life (QoL), metabolic stress and nutritional response after PD.

The risk category for this study is Category A according to ClinO, Art. 61. The health-related intervention submitted to the clinical trial involves only minimal risks and burdens. The risks are linked to the nasojejunal tube (poor tolerance, nausea, ...). The investigators evaluate these risks as minimal. Moreover, the nursing staff is used to this type of nasojejunal tube as it is often routinely used in visceral surgery and in our division.

### **3 STUDY OBJECTIVES AND DESIGN**

#### **3.1 Hypothesis and primary/secondary objectives**

The hypothesis is that EEN after PD might decrease the postoperative complications compared to oral nutrition as patients undergoing PD often are malnourished. The primary objective is to assess the impact of EEN on postoperative morbidity, according to the CCI, after PD in patients at nutritional risk with a NRS  $\geq 3$ .

The secondary objective is to evaluate the impact of EEN on major postoperative complication, according to Clavien classification, specific complications, length of stay, readmission rates, QoL, metabolic stress and nutritional response after PD in patients at nutritional risk with a NRS  $\geq 3$ .

### 3.2 Primary and secondary endpoints

The primary endpoint measuring postoperative morbidity will be assessed using the CCI within 90 postoperative days.

Secondary endpoints are the following:

- Most severe postoperative complications will be measured using the Clavien classification within 90 postoperative days.
- Specific complications of PD will be recorded:
  - SSI, further divided into 'superficial', 'deep' and 'organ-space' according to the specific anatomic involvement and the Centers for Disease Prevention definition.
  - POPF are classified into three grades, A, B and C, according to the consensus of the International Study Group for Pancreatic Surgery (ISGPS).
  - DGE, which is classified into three grades, A, B and C, according to the consensus of the ISGPS.
  - PPH, which is also classified into three grades, A, B and C, according to the consensus of the ISGPS.
  - Biliary fistula (no standard definition)
  - Gastrojejunal anastomosis fistula (no standard definition)
  - Pancreatitis (no standard definition)
- Length of stay will be measured from operative day until discharge.
- Readmissions will be counted until postoperative day 90.
- Patients' QoL will be assessed by the EORTC (European Organisation for Research and Treatment of Cancer) QLQ-C30 questionnaire. This questionnaire will be filled 4 times: at preoperative consultation or admission, at patient's discharge, between the 4th and 6th postoperative week and on POD 90 (via phone call).
- The subjective tolerance of EEN will be assessed daily during the first 7 postoperative days, using a visual analogue scale (0-10). Objective tolerance will be assessed by the amount of EEN as a percentage (tolerated/total amount of EEN required).
- Time required (in days) to reach respectively 50% and 100% of the daily caloric targets required (30 kcal/kg/day if BMI <30 kg/m^2 and 25 kcal/kg/day if BMI ≥30 kg/m^2, protein target: 1.5 g/kg/day).
- Metabolic response to EEN will be assessed with biological measurements preoperatively and twice weekly (currently already measured, according to our PD care map):
  - C-Reactive Protein (CRP) and procalcitonin
  - Simple blood count, coagulation
  - Electrolytes: sodium, potassium, calcium, magnesium, phosphate
  - Creatinine, urea, blood glucose, liver and pancreatic function tests, prealbumin,

[figure not shown]

albumin, triglycerides

- Various malabsorption due to PD surgery: measurements will be made twice, once before surgery and once between the 4th and 6th postoperative week during the follow-up visit. As PD might induce duodenal and pancreatic insufficiencies postoperatively due to the resection of the duodenum and the pancreatic head, it is presently unknown if EEN might have an effect on these insufficiencies by improving the overall nutritional state and the mucosal trophicity of the small bowels.
  - Duodenal insufficiency: folate, magnesium, calcium, iron, ferritin, transferrin saturation
  - Exocrine pancreatic insufficiency: malabsorption of fat soluble vitamins: vitamin D (with calcium/phosphate balance and parathormone) and vitamin E
  - Endocrine pancreatic insufficiency: due to risk of developing a secondary diabetes, HbA1c (glycated hemoglobin) will be measured.
- Body measure using bioelectrical impedance analysis (BIA) and muscle strength using handgrip will be measured preoperatively, on discharge day, and on the first follow-up visit.
- Resting energy expenditure will be measured on POD 5 using indirect calorimetry.

Each of these endpoints will be measured in the study (EEN) and control (oral nutrition) groups.

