### 3.4. Study intervention

After PD, patients will be randomized to receive either EEN or oral nutrition. Patients included in the EEN arm will receive, in addition to oral nutrition based on the current care maps, enteral nutrition according to the following scheme that was established in accordance with nutritionists:

- Six hours after the operation, a low flow enteral feeding will be initiated (21 ml/h, 250 ml/12h), and based on a Isosource® Energy Fibre solution (hypercaloric, 400 kcal).
- If the tolerance is subjectively good, with a visual analogue scale  $\leq 4/10$ , the flow will be increased on first postoperative day (POD), at the flow of 42 ml/h (500 ml/12h, 800 kcal).
- On POD 2: increased flow to 62.5 ml/h (750 ml/12h, 1200 kcal)
- On POD 3: increased flow to 83.5 ml/h (1000 ml/12h, 1600 kcal)

If the tolerance is not satisfactory ( $>4/10$ ), the current flow will be maintained 24 hours more, decreased or put on hold for a couple of hours (depending on the symptoms of the patient), and increased the next day if tolerated until the maximum of 1000 ml/12h.

The diet will be infused over 12 hours with a pump and controlled flow rate. EEN will be continued

until oral food intake will have reached more than 50% of nutritional requirements. Daily nutritional requirements will be defined as 30 kcal/kg if BMI <30 kg/m^2 and 25 kcal/kg if BMI ≥30 kg/m^2 (protein target: 1.5 g/kg/day). The oral intake will be assessed by the dietitian.

If a patient in the EEN group loses or displaces its nasojejunal tube (vomiting, accidental removal), a new probe will be replaced under endoscopic control by the gastroenterologist. If that happens a second time, another attempt to put the nasojejunal tube will not be made (the patient will remain in the study). In the same previous scenario (nasojejunal tube expulsion), and if the patient suffers from DGE, a nasogastric tube will be installed at the same time. If the patient suffers from DGE and the nasojejunal tube is in place, a nasogastric suction tube will be installed in addition, and enteral feeding will be continued. Parenteral nutrition will be used to complete the missing caloric needs. In the control group (without nasojejunal tube), in case of DGE, a nasogastric suction tube will be installed (the patient will remain in the study).

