#### **4.4 Withdrawal and discontinuation**

Patients will be withdrawn from the study if they leave the operation room with only a suction nasogastric tube in place or in case of withdrawal of informed consent, non-compliance to the study protocol, or due to safety concerns. Participants will not be replaced and considered as dropouts. Study data already collected on a participant until the time of withdrawal will still be used for analysis in a coded manner. No further data will be collected however from that time onwards.

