## **5 STATISTICS AND METHODOLOGY**

### **5.1. Statistical analysis plan and sample size calculation**

A statistician was involved in the study design and estimate of the sample size.

Null hypothesis  $H_0$ : EEN has no effect on postoperative complications (CCI) in the population (and therefore the observed effect is entirely due to chance):  $p_2 = p_1$

Scientific hypothesis  $H_1$ : EEN has an effect on postoperative morbidity (CCI) in the population (and therefore the observed effect is not entirely due to chance):  $p_2 > p_1$

According to a previous randomized trial including a series of PD and assessing a realimentation process (enteral vs. parenteral), the mean CCI was impacted of about 30% (32.8 vs. 24.2). Another study reported a mean CCI of 38 after PD.

Based on the above results, we hypothesize that EEN will reduce by 30% a mean CCI of 35 (+/- 20) of the oral nutrition group. We will therefore expect a mean CCI for the treatment group (EEN) of 24.5 (SD 20). In this superiority study, for a power of 80% and a significance level of p-value  $\leq 0.05$  (two-sided alpha), we will therefore need 57 patients per group according to the sample size calculation. Nevertheless, we will increase the sample size to a total of 144 patients to take into account 20% of drop-outs (e.g., due to non realization of pancreatoduodenectomy or consent withdraw) at 90 days (primary endpoint evaluation). We will therefore need to enroll 72 patients per group in the trial.

The study will be closed once the required 144 patients will be included. No interim analysis will be performed.

Normality of distribution will be determined by the Kolmogorov-Smirnov test and quantile-quantile plots of dependent variables for all continuous variables.

We will use a Student *t*-test to evaluate if the primary outcome (CCI) can significantly be reduced by EEN compared to the control group (comparison of mean CCI hypothesizing a normal distribution). For the analysis of all secondary endpoints, we will also use *t*-tests or chi-squared tests based on the variable types. Regarding the questionnaires filled 4 times during the study, tests specific to repetitive ordinal measures will be used.

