The analysis will be based on the intention-to-treat method and not per protocol. We will perform an intention-to-treat analysis so that all patients being intended to treat will be analyzed in the statistics independently. All patients will therefore be analyzed according to the group in which they were initially randomized.

Blocked randomization will be done using a computerized algorithm via REDCap by a research coordinator (different from the person who included the patient) the day before surgery. The proportion of "study" (EEN) and "control" (oral nutrition) subjects will be 1:1 (mix of variable block sizes of 4, 6, and 8 patients, randomly selected). Before surgery, only the responsible surgeon will know the allocation group. Postoperatively, the inclusion in the different groups will be known by the caregiver team and the patient, as it is not possible to blind the intervention (nasojejunal tube).

The investigators, the outcome adjudicators, and the data analysts will be blinded (allocation concealment).

The statistical package used for analysis will be SPSS version 26 (IBM Corp., Armonk, NY, USA).

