## 5.2. Handling of missing data and drop-outs

In case of missing data among variables other than endpoints (adjustment variables, >5% of expected data) we will consider the use of the multiple imputation technique. This process will be performed multiple times (e.g., 10-20 times) to combine multiple data sets to produce one final data sets replacing the missing data.

A 20% drop-out was considered in the sample size calculation.

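### Time to the caloric targets is assigned to a t-test with no rule for patients who never reach the target; this matters mainly for the 100% target

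*Protocol*

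**What the plan says.** Section 3.2 of the protocol defines the endpoint as "Time required (in days) to reach respectively 50% and 100% of the daily caloric targets required", with the target set at 30 kcal/kg/day, or 25 kcal/kg/day from a BMI of 30. The same section says each endpoint is measured in both arms.

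Section 5.1 fixes the test: "For the analysis of all secondary endpoints, we will also use *t*-tests or chi-squared tests based on the variable types". The statistical considerations in the synopsis say the same. One exception follows in 5.1: "Regarding the questionnaires filled 4 times during the study, tests specific to repetitive ordinal measures will be used". A time in days is a continuous variable and is not excepted, so it goes to the t-test.

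Three further statements bear on patients without a value:

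- Section 5.1, on the analysis set: "All patients will therefore be analyzed according to the group in which they were initially randomized".
- Section 5.2, on missing data, limits imputation to non-endpoint variables: "In case of missing data among variables other than endpoints (adjustment variables, >5% of expected data".
- Section 4.4, on patients who withdraw: "No further data will be collected however from that time onwards".

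**The concern.** Time to a feeding target is a time-to-event outcome. Some patients will leave observation before the event, and for them the plan has neither a number of days nor a rule that assigns one. A t-test needs a number for every patient it includes, so as the text stands it would be run on those who reached the target.

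That subset depends on the treatment. If EEN brings more slow patients to target, their late times enter the EEN mean while comparable controls are left out. If EEN shortens the stay, which section 7.2 names as a possible benefit, late reachers in that arm are cut off and its mean falls with no change in feeding. The first mechanism hides a real effect and the second can create one. Nutritional response is a named secondary objective, and this endpoint measures directly whether EEN delivers calories sooner.

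**Working it through.** **1. The protocol's own figure.** The only sample size stated is for the CCI: difference 10.5, SD 20, two-sided 5%, power 80%. The normal-approximation formula gives 57 per group, and 57/0.8 = 71.25, rounded up to 72, so 144 in total. This reproduces. No figure is stated for the time-to-target endpoint.

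**2. Can a patient miss the target?**

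- *50% target.* Under section 3.4, EEN continues "until oral food intake will have reached more than 50% of nutritional requirements". In both arms parenteral nutrition may start from POD 3 when intake is below 50% for 24 hours, and it runs until intake without it exceeds 50%. A missing 50% time would therefore need death, withdrawal, or discharge while still on support. Few patients should be affected.
- *100% target.* No support rule carries a patient to 100%. The maximum tube supply is 1600 kcal, which meets 30 kcal/kg up to 1600/30 = 53 kg and 25 kcal/kg up to 1600/25 = 64 kg. Section 4.3 adds two oral supplements, listed at 280 kcal. Read as 280 kcal in total, tube plus supplements give 1880 kcal, enough for 1880/30 = 63 kg. Read as 280 kcal each, they give 2160 kcal, enough for 72 kg. Heavier EEN patients, and all controls, depend on food or parenteral calories. The expected stay is about 14 days (section 4.3). Missing 100% while observed is plausible, but the protocol gives no attainment rate.

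**3. Size, on assumed inputs.** Only the 57 per arm and the 14-day mean stay come from the protocol. The rest is assumed: control time to target T = 2 + exponential(mean m) days; EEN reaches target at 1.5 times the control rate, so its mean is m/1.5; discharge is log-normal (log-SD 0.5, mean 14 days) and independent of T unless stated. The t-test uses patients with T no later than discharge. The log-rank test uses everyone, censored at discharge.

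Power, t-test against log-rank:

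- m = 3 (control mean day 5, about 8% of controls not reaching): about 41% against 55%. With correlation 0.5 between feeding and discharge: 49% against 57%.
- m = 8 (control mean day 10, about 30% not reaching): about 18% against 46%. The true difference of 8 − 8/1.5 = 2.7 days shrinks to under 1 day among reachers.
- m = 14 (control mean day 16, about 48% not reaching): about 10% against 38%.

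False rejection by the t-test when feeding is identical but the EEN stay averages 11 instead of 14 days:

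- m = 3: about 7%, and about 5% with correlation 0.5.
- m = 8: about 10% to 11%, against 5% to 6% for log-rank.

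**4. A second model.** Weibull times (shape 1.5), observation ending at day 14, 57 per arm:

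- Medians 4 (EEN) and 6 (control): 1% and 8% not reached; t-test 65% against log-rank 88%.
- Medians 8 and 12: 20% and 42% not reached; a true difference of 4.6 days becomes 0.7 among reachers; 14% against 78%.
- Equal medians of 8: 20% not reached in each arm, no bias, and both tests reject in about 5%.

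**The case against.** The strongest reply has four parts.

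- *A t-test need not drop anyone.* Non-reachers could be given a value such as the end of observation, and such a rule is often left to the SAP. This is fair: a reader might infer that the t-test can only ever use reachers, and the protocol does not say so. It does name the test, it excludes endpoints from imputation, and it states no value for non-reachers. Assigning everyone the end of observation would still treat a censored time as an observed one.
- *The 50% target is largely safe.* This stands. A reader might take both targets to be equally affected, but the support rules in section 3.4 point the other way.
- *The larger power gaps come from pessimistic inputs.* This also stands. The protocol plans a full-portion diet on POD 4, supplements from POD 1 and up to 1600 kcal by tube from POD 3, so attainment may be quick. With about 8% of controls not reaching, the loss is modest.
- *Appendix 1 proves little.* A reader might cite its lack of post-discharge intake measurement as evidence of censoring. It lists no intake measurement at any time, including in hospital, so its silence after discharge shows nothing specific.

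It is also true that this is one of many secondary endpoints, is absent from the synopsis endpoint list, and drives no sample size or decision rule.

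**Conclusion.** The point holds in a limited form. The protocol itself assigns a possibly censored time to a t-test and gives no rule for patients without a value. The likely consequence is a comparison of reachers only, at odds with the commitment to analyse everyone as randomised. It concerns mainly the 100% target.

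The comparison may lose power, or be biased, if attainment or length of stay differs between arms. If both are equal, the arm difference need not be biased. A reader might conclude that the result will be distorted, or will point the wrong way; the documents do not support that, since they give no attainment rates and no joint behaviour of feeding and discharge. Across the assumed range with 57 per arm and a 14-day mean stay, the power loss runs from about 14 percentage points (41% against 55%) to about 28 (10% against 38%), and is smaller still (49% against 57%) when quick feeding goes with earlier discharge. False rejection with a shorter EEN stay runs from about 5% to 11%.

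This is worth correcting because it is cheap. It does not threaten the trial's main conclusion.

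**What to change.** In section 5.1, and in the matching synopsis sentence, exempt the two time-to-target endpoints from the t-test. Analyse all randomised patients by cumulative incidence of reaching each target, counted from surgery, with death as a competing event and a log-rank type test stratified by centre, since randomisation is stratified by centre. State that withdrawal before target is censored. Censor discharge before target in the main analysis and count it as target not reached in a sensitivity analysis, because discharge is probably related to feeding and plain censoring may then be informative.

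The cost is about one sentence of protocol text and slightly more analysis work on the same intake data. No patients are added, and the CCI analysis and the total of 144 stay as they are.
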